#### Secondary endpoints

1. *Residual Cancer Burden (RCB)*

Residual Cancer Burden (RCB) is measured as four ordered categories (RCB-0 which corresponds to pCR, RCB-I, RCB-II, and RC-III) at histopathological assessment of the surgical specimen. An ordinal regression model, adjusting for biological tumour type (stratification factor in the randomization), will be used to analyse differences between the treatment arms. If the proportional odds assumption of the model is violated, a nominal regression model or a generalized logistic model will be used instead if appropriate.

1. *Objective tumour response*

Response Evaluation Criteria in Solid Tumours (RECIST) will be applied in order to assess change in radiological tumour size (%) from baseline to pre-surgery imaging. RECIST criteria classify response into four ordinal outcome categories: complete response, partial response, stable disease and progressive disease (see page 18)^31^. An ordinal regression model, adjusting for biological tumour type (stratification factor in the randomization), will be used to analyse differences between the treatment arms. If the proportional odds assumption of the model is violated, a nominal regression model or a generalized logistic model will be used instead if appropriate. Tumour size at histopathological assessment of the surgical specimen may be included in comparative analyses. Mean difference in reduction of tumour size between treatment arms will be analysed with an ANOVA, including biological subtype as a factor in the model.

1. *Survival outcomes*

All-cause, breast cancer-specific and recurrence-free survival will be analysed at 2, 5 and 10 years. Contralateral breast cancer is not regarded an event. Difference in time-to-event outcomes between treatment arms will be compared. The mortality outcomes are defined as time from date of randomisation to death (from any cause or breast cancer as underlying cause, respectively) or censoring at end of follow-up. For recurrence-free survival, the outcome is measured as time from date of randomisation to breast cancer relapse or censoring at end of follow-up. Survival estimates after 2, 5 and 10 years of follow-up will be compared using Kaplan-Meier estimates. Furthermore, a Cox regression model, adjusting for biological subtype will also be used.

1. *Health-related quality of life*

All health-related quality of life outcomes are measured as scores that range from 0 to 100, hence the outcomes are continuous. Both the global QoL score as well as the 17 subscales (8 scales reflecting symptoms and 9 reflecting function) will be assessed at four time points: baseline, pre-surgery, 1 and 2 years after surgery. To evaluate QoL scores at each time point both within and between the treatment groups, a mixed model for repeated measures (MMRM) will be used. Treatment, visit, treatment visit interaction and stratification factor biological tumour type will be included in the model as fixed effects, and patient as a random effect. An unstructured covariance matrix will be used to model the within-subject error. If the fit of the chosen structure fails to converge, the following covariance structures will be evaluated, in order, until convergence is reached: toeplitz with heterogeneity, autoregressive with heterogeneity, toeplitz, autoregressive and compound symmetry. Furthermore, differences in change from baseline between the treatment arms will be assessed at each time point by constructing relevant contrasts of the estimated regression coefficients.

1. *Self-reported physical activity*

Physical activity is reported using the Godin-Shephard Leisure-Time Physical Activity Questionnaire (GSLTPAQ) as total minutes per week of training in three intensity levels (light, moderate and intensive) and for weight training. Hence, the outcome is continuous. A mixed model for repeated measures (MMRM) will be used to assess physical activity at four different time points: baseline, pre-surgery, 1 and 2 years after surgery). The model will include treatment, visit, treatment-visit interaction and the stratification factor biological tumour type as fixed effects, and patient as a random effect. An unstructured covariance matrix will be used to model the within-subject error. If the fit of the chosen structure fails to converge, the following covariance structures will be evaluated, in order, until convergence is reached: toeplitz with heterogeneity, autoregressive with heterogeneity, toeplitz, autoregressive and compound symmetry. Physical exercise will be assessed both within and between the treatment groups. Furthermore, differences in change from baseline between the treatment arms will be evaluated at each time point by constructing relevant contrasts of the estimated regression coefficients.

An additional analysis, using a dichotomous outcome that classifies patients as *active* and *insufficiently active* based on a score generated from GSLTPAQ, will be performed. Here, a generalized linear mixed model (GLMM) for repeated measures with a logit link function will be implemented. Activity will be assessed at baseline, pre-surgery and at 1- and 2-year follow-up, both within and between treatment arms. An unstructured covariance matrix will be used to model the within-subject error. If the fit of the chosen structure fails to converge, the following covariance structures will be evaluated, in order, until convergence is reached: toeplitz with heterogeneity, autoregressive with heterogeneity, toeplitz, autoregressive and compound symmetry.

1. *Toxicity-related outcomes*

The following toxicity-related outcomes will be assessed: a, chemotherapy completion rates, b, number of unplanned hospital admissions, c, cognitive function (measured at baseline and one year after surgery), d, cardiotoxicity and e, sick leave.

1. Chemotherapy completion rates, i.e. the proportion of participants receiving the planned number of treatments including potential adjuvant chemotherapy, is a dichotomous outcome (yes/no). Both neoadjuvant and adjuvant treatment will be assessed separately (regarded as two independent measurements) in multivariable logistic regression models, adjusting for biological tumour type (stratification factor in the randomization). The treatment effect will be assessed in terms of a resulting odds ratio and a complementary Wald test.
2. For the count outcome number of unplanned hospital admissions, we will use a Poisson regression model, adjusting biological tumour type. If overdispersion is present, a negative binomial regression will be considered instead. Results from the final model (Poisson or negative binomial, whichever fits the data best) will be presented as incidence ratios (IR) together with confidence intervals and a Wald test of the treatment effect.
3. Objective cognitive dysfunction is measured by an online neuropsychological test (Amsterdam Cognition Scan) at baseline and 1-year follow-up. The total Amsterdam Cognition Scan (ACS) score, calculated as the mean of the (reversed) z-scores of all main online neuropsychological outcome measures, will be of primary interest. Furthermore, separate z-scores of the cognitive tests will also be assessed. Hence, the measured cognitive dysfunction outcomes, measured at baseline and at 1-year follow-up, are continuous variables. A mixed model for repeated measures (MMRM) will be used to assess change from baseline of ACS scores, which is the primary interest. The model will include treatment, visit and the stratification factor biological tumour type as fixed effects, and patient as a random effect. An unstructured covariance matrix will be used to model the within-subject error. If the fit of the chosen structure fails to converge, the following covariance structures will be evaluated, in order, until convergence is reached: toeplitz with heterogeneity, autoregressive with heterogeneity, toeplitz, autoregressive and compound symmetry. ACS scores will be assessed both within and between the treatment groups.
4. Cardiovascular toxicity is a dichotomous outcome (yes/no) that will be evaluated only in the subgroup of patients with HER2-positive tumours who are treated with anti-HER2 therapies (approximately 30% of the study population). A multivariable logistic regression model, adjusting for biological tumour type will be used to assess differences between the treatment arms.
5. Sick leave is a patient-reported singular measurement at pre-surgery and at 1- and 2-year follow-up (% sick leave). Mean sick leave proportions will be compared between the treatment arms at each time point using a mixed model for repeated measures (MMRM). Treatment, visit, treatment visit interaction and the stratification factor biological tumour type will be included in the model as fixed effects, and patient as a random effect. An unstructured covariance matrix will be used to model the within-subject error. If the fit of the chosen structure fails to converge, the following covariance structures will be evaluated, in order, until convergence is reached: toeplitz with heterogeneity, autoregressive with heterogeneity, toeplitz, autoregressive and compound symmetry. Additionally, since the outcome is most likely not normally distributed, a non-parametric Kruskal-Walllis test will be performed at each time as a sensitivity analysis.
6. *Device-measured physical activity level*

Several continuous outcome measures from the Fitbit activity tracker will be assessed: 1) METs (metabolic equivalents) in low, medium and high intensity activities, respectively, 2) step counts per day and 3) daily active minutes. The main interest is to see if there is a difference between the treatment arms regarding change of physical activity from baseline to pre-surgery (i.e. after intervention and chemotherapy), but also at 1-year follow-up. A mixed model for repeated measures (MMRM) with treatment, visit and the stratification factor biological subtype as fixed effects, and patient as a random effect. An unstructured covariance matrix will be used to model the within-subject error. If the fit of the chosen structure fails to converge, the following covariance structures will be tried, in order, until convergence is reached: toeplitz with heterogeneity, autoregressive with heterogeneity, toeplitz, autoregressive and compound symmetry. Additionally, heart rates at equivalent exertion levels (assessed on the Borg scale) during physical activity will be explored.

1. *Muscle strength*

The muscle strength is measured on a continuous score on each arm and leg. The main interest is to see if there is a change in strength after intervention, i.e. change from baseline to pre-surgery. A mixed model for repeated measures (MMRM) with treatment, visit and the stratification factor biological tumour type as fixed effects, and patient as a random effect. An unstructured covariance matrix will be used to model the within-subject error. If the fit of the chosen structure fails to converge, the following covariance structures will be tried, in order, until convergence is reached: toeplitz with heterogeneity, autoregressive with heterogeneity, toeplitz, autoregressive and compound symmetry.

1. *Cardiorespiratory fitness*

The Åstrand submaximal cycle test renders a continuous outcome. The main interest is to see if there is a change in cardiorespiratory fitness after intervention, i.e. change from baseline to pre-surgery. A mixed model for repeated measures (MMRM) with treatment, visit and the stratification factor biological tumour type as fixed effects, and patient as a random effect. An unstructured covariance matrix will be used to model the within-subject error. If the fit of the chosen structure fails to converge, the following covariance structures will be tried, in order, until convergence is reached: toeplitz with heterogeneity, autoregressive with heterogeneity, toeplitz, autoregressive and compound symmetry.

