# Background

***Use of neoadjuvant (preoperative) chemotherapy in breast cancer***

Neoadjuvant chemotherapy (NACT) has a history of being reserved for non-operable, locally advanced breast cancer (BC) but is increasingly used for patients with early BC. It is strongly recommended by national^1^ and international^2^ guidelines especially in the triple-negative (TNBC) and HER2-positive BC subtypes, and in case of lymph node metastases. In Sweden, 14% of all newly diagnosed early BC patients suitable for surgery (1041 out of 7289 individuals according to the National Breast Cancer Register) received NACT in 2019 (22% in Stockholm), while this figure was 35% (Stockholm 45%) for TNBC and HER2-positive BC, and 50% (Stockholm 62%) for all clinically node-positive BC. Combining lymph node metastases and tumour subtype, the rate of NACT was as high as 68% (Stockholm 80%) in clinically node-positive TNBC and HER2-positive BC in 2019.

The best proof of NACT efficacy is pathological complete response (pCR), i.e. the absence of residual invasive tumour in the breast and the axillary lymph nodes. Especially in the above-mentioned tumour subtypes TNBC and HER2-positive breast cancer, published pCR rates are high (50.7% in TNBC and 63.7% in HER2-positive, oestrogen receptor (ER)-negative BC) and strongly predict improved survival^3^. In luminal BC (ER-positive, HER2-negative), published pCR rates are substantially lower (10.8% if HER2 negative, 29.4% if HER2 positive)^3^ which underlines the need for novel regimens including anti-endocrine strategies. Today, pCR is frequently used as surrogate endpoint in oncological pharmaceutical trials focusing on new compounds often in combination with the current standard of care (traditionally chemotherapy and/or targeted therapies with anti-HER2 and anti-ER drugs, but now also immunotherapy, CDK4/6 inhibitors and drug-antibody conjugates).

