## Estimated sample size and power

Patients will be randomized in a 1:1 fashion. It is anticipated that the rate of the primary endpoint pCR will be approximately 30% in the control arm. We aim to increase the rate of pCR in the experimental arm to 40%, i.e. a 10 percentage points increase, which is regarded clinically relevant since it would translate into improved disease-related outcomes. With a power of 80% and an alpha of 5%, a total of 712 patients have to be included; 356 in each arm. Accounting for a drop-out of 10%, we aim to include 790 patients. Stratification at the moment of computerized randomization will be done based on site of treatment (hospital) and biological tumour subtype (ER+HER2-, ER+HER2+, ER-HER2+, ER-HER2-).

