#### Reporting

For the secondary outcomes, the differences between the treatment arms will be reported as an effect measure (e.g. odds ratio or mean difference) together with a complementary confidence interval and a two-sided statistical test of the effect parameter. A Bonferroni corrected significance level will be used.

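### RCB and RECIST response: a proportional-odds failure in the tumour-type covariate alone can replace the single ordered treatment comparison with a nominal model

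*Protocol*

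**What the plan says.** The Protocol, Statistical analysis plan, Secondary endpoints, treats RCB as four ordered classes and says of the radiological endpoint: "RECIST criteria classify response into four ordinal outcome categories: complete response, partial response, stable disease and progressive disease". Both get the same first-choice analysis, an ordinal regression of treatment adjusted for biological tumour type.

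Both also get the same fallback: "If the proportional odds assumption of the model is violated, a nominal regression model or a generalized logistic model will be used instead". The sentence closes by limiting this to cases where it is appropriate. No diagnostic, threshold or criterion of appropriateness is given. The second named alternative is not defined. It could mean unordered generalized logits, or a generalized ordered logit that keeps the order.

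The Reporting section states: "the differences between the treatment arms will be reported as an effect measure (e.g. odds ratio or mean difference) together with a complementary confidence interval". This applies to all secondary endpoints. The section also asks that the effect parameter be tested two-sided, at a Bonferroni level whose divisor is not stated.

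**The concern.** The fallback depends on the proportional-odds assumption of the model, and that model contains tumour type as well as treatment. Tumour type is a very strong predictor of response. In the Background, "published pCR rates are high (50.7% in TNBC and 63.7% in HER2-positive, oestrogen receptor (ER)-negative BC", against 10.8% and 29.4% in ER-positive disease without and with HER2. A covariate this strong can shift the pCR cut by a different amount from the RCB-III cut, and so fail the check, for reasons unrelated to exercise. A valid one-parameter treatment comparison does not need tumour type to be proportional.

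If the nominal model is then used, three things follow:

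- RCB-III no longer counts as worse than RCB-I.
- One treatment parameter becomes three, and none of them is designated as the effect parameter that Reporting asks for.
- If the treatment effect is in fact proportional, power is lost on the first two secondary endpoints.

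**Working it through.** **1. The plan's own figure.** Under Estimated sample size and power: "It is anticipated that the rate of the primary endpoint pCR will be approximately 30% in the control arm", with a target of 40%, and "With a power of 80% and an alpha of 5%, a total of 712 patients have to be included; 356 in each arm".

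n per arm = [1.96·√(2·0.35·0.65) + 0.8416·√(0.30·0.70 + 0.40·0.60)]² / 0.10² = 355.9, so 356 per arm and 712 in total. This agrees. The marginal odds ratio is (0.40/0.60)/(0.30/0.70) = 1.556. No power is stated for RCB or RECIST.

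**2. Can tumour type alone trip the check?** The protocol gives subtype rates at the pCR cut only. Assume, for illustration, that residual disease splits 20/55/25% over RCB-I/II/III in every subtype. Compare triple-negative with ER+HER2-:

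- pCR cut: logit(0.507) − logit(0.108) = 0.03 − (−2.11) = 2.14.
- RCB-III cut: the RCB-III shares are 0.25·0.493 = 0.123 and 0.25·0.892 = 0.223, so logit(0.877) − logit(0.777) = 1.96 − 1.25 = 0.71.

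The tumour-type effect is far from proportional here, whatever treatment does.

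Trials of 712 patients were simulated with the Background pCR rates and several assumed splits under which tumour type is not proportional. A 5% whole-model check rejected in 69% to 100% of trials, and a check of the treatment term alone in 3% to 8%. When the subtype effects were made proportional, the whole-model check rejected in only 6% to 7%. The frequency therefore depends on the unknown split.

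**3. What a switch costs when the treatment effect is proportional.** Inputs:

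- N = 712, allocated 1:1.
- Subtype mix 45/18/12/25% (ER+HER2-, ER+HER2+, ER-HER2+, triple-negative). This is assumed, but it matches the protocol's figure of about 30% HER2-positive and gives a mean pCR of 30.5%.
- The 20/55/25% split above (assumed).
- Alpha of 0.05, or 0.05/9 = 0.0056. The divisor is assumed from the nine listed secondary endpoints.
- A joint 3-df test of treatment in the nominal model (assumed).

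Noncentrality: λ = (ln OR)² · (N/12) · k. Here k is the subtype-weighted mean of 1 − Σp̄³, and p̄ is the category probability averaged over the arms. For OR 1.556, k = 0.840 and λ = 0.195 · 59.33 · 0.840 ≈ 9.7. Power is the upper tail of a noncentral chi-square with 1 or 3 df at this λ.

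| OR | λ | 5%: 1 df / 3 df | loss | 0.05/9: 1 df / 3 df | loss |
| --- | --- | --- | --- | --- | --- |
| 1.3 | 3.5 | 46% / 31% | 15 | 18% / 10% | 8 |
| 1.4 | 5.7 | 66% / 49% | 17 | 35% / 21% | 14 |
| 1.556 | 9.7 | 88% / 75% | 13 | 64% / 45% | 19 |
| 1.74 | 15.2 | 97% / 92% | 5 | 87% / 73% | 14 |

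An OR of 1.74 is the within-subtype value that raises overall pCR by 10 points under this mix. At equal λ the loss cannot exceed 17 points at 5% or 19 points at 0.05/9.

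A subtype-adjusted simulation (300 runs per setting, two assumed splits) agrees. The loss was 5 points at OR 1.74 and 5%, 15 points at OR 1.74 and 0.05/9, and 14 to 20 points at OR 1.4. The 20 lies within Monte Carlo error of the analytic 17.

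**4. When the effect is not proportional.** Simulations of about 250 runs per scenario, tested at 5%:

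- Log odds ratios falling from 0.56 to 0.42 to 0.28 across the cuts: 79% ordered, 76% nominal.
- An effect that vanishes at the RCB-III cut: 60% ordered, 80% nominal.

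**The case against.** Several stronger readings are tempting, and the protocol does not support them.

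- *The order is dropped whenever the check fails.* The text limits the switch to where it is appropriate, and one named alternative may be an ordered model. The fair statement is that the rule allows the order to be dropped, without a criterion. A generalized ordered model with cut-specific treatment effects would still give three treatment parameters.
- *Tumour type will usually trigger it.* Large subtype differences in pCR concern one cut only and do not by themselves imply non-proportionality. For RECIST there are no subtype figures at all.
- *The loss is a property of the planned rule.* The losses compare always ordered with always nominal. The average loss under the rule is smaller, because the switch does not happen in every trial.
- *The data-driven choice inflates type I error.* In the simulations the switching rule rejected in 4% to 8% of null trials at 5%, which shows no material inflation at that precision.
- *RECIST is left without a single effect.* The protocol also plans an ANOVA of the reduction in tumour size, which the fallback does not touch.

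It is also fair to say that the diagnostic and its threshold may be left to a separate statistical analysis plan, and that keeping a common odds ratio under non-proportionality is a trade-off. But the trigger and the nominal replacement are written into the protocol, so they are not merely unspecified detail.

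**Conclusion.** The point holds as a badly fixed fallback rule on two secondary endpoints. The trigger covers the whole model. The permitted nominal replacement ignores the order and does not fit the single effect parameter under Reporting. Tumour type can readily set it off while treatment is proportional, depending on a residual-disease split that the protocol does not give.

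If a switch to the nominal model occurs, the treatment effect is proportional and a joint 3-df test is used, about 5 to 19 points of power are lost at 712 patients. For an odds ratio of 1.556 the loss is about 13 points at 5% and 19 points at 0.05/9. The joint test, the divisor of 9, the subtype mix and the RCB split are assumptions. The primary pCR analysis and the sample size are not affected.

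**What to change.** For RCB and RECIST response, replace the fallback sentence with wording to this effect:

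*The treatment effect is estimated by an ordinal regression with a single treatment odds ratio, in which biological tumour type is not constrained to be proportional (cut-points specific to tumour type, or a partial proportional-odds model). The treatment odds ratio, its confidence interval and its test are the reported result. Proportional odds is checked for the treatment term only. If that check fails, the three cut-specific treatment odds ratios are reported as well, and any nominal model is a sensitivity analysis.*

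This changes wording only and needs no new data. With four tumour types and three cuts the model has 12 cut-points. If a category is rare within a subtype, the partial proportional-odds form is the simpler choice. The downside is small: the ordered test is weaker than the nominal one if the effect vanishes at the worse categories, a case that the primary pCR analysis largely covers.

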## Population

Clinically T1-3, N0-2 BC patients scheduled for NACT and surgery with curative intent and fulfilling all inclusion criteria and no exclusion criteria as listed below. Patients with oligometastases scheduled for such curative treatment are eligible. Baseline stratification is performed based on treating hospital and biological tumour subtype (ER+HER2-, ER+HER2+, ER-HER2+, ER-HER2-) prior to randomization.

Eligible patients are identified at pre-NACT multidisciplinary team conferences and then receive information about the trial by their oncologist or surgeon, avoiding undue delays. Informed consent is mandatory before randomization and can be obtained by physician or nurse with the appropriate delegation. All participants will undergo standardised tests of physical condition and strength before start of NACT and after NACT but before surgery.

| **Inclusion criteria** | **Exclusion criteria** |
| --- | --- |
| - Patients with primary invasive breast cancer cT1-T3 cN0-2 - Full tumour biology available before initiation of NACT (ER, PR, HER2, tumour grade, and Ki67) - Written informed consent - Age ≥ 18 years | - Bilateral invasive breast cancer - Pregnancy or breast-feeding - The presence of musculoskeletal, neurological, respiratory, metabolic or cardiovascular conditions that may prevent safe completion of the exercise and testing demands of the study - Currently performing equal to or more than 150 mins of moderate to high intensity aerobic exercise and 2 sessions per week of moderate intensity resistance exercise (WHO criteria) |

In case of pre-term abortion of NACT, participants may remain on the trial. Participants who have not received at least four treatment cycles (three weekly treatments of e.g. paclitaxel correspond to one treatment cycle) as NACT are excluded from per-protocol analyses (see statistical analysis plan).

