## Outcomes, Variables and measures

The **primary endpoint** pCR is measured by histopathological assessment according to the TNM classification of the American Joint Committee on Cancer (ypT0/is ypN0) after breast and axillary surgery (approx. 5 months after initiation of NACT, according to standard of care).

In order to ensure congruence in assessment of pCR between study sites, a central review of histopathological tumour slides will be performed for all included cases. Routine slides will be collected from participating sites and digitally scanned for central pathology review at Karolinska University Hospital in Stockholm. Slides will thereafter be returned to the study sites.

The **secondary** endpoints are:

1. Residual Cancer Burden (RCB), calculated using primary tumour bed area (mm x mm), overall cancer cellularity (%), percentage of cancer that is in situ disease (%), number of positive lymph nodes and diameter of largest nodal metastasis (<http://www3.mdanderson.org/app/medcalc/index.cfm?pagename=jsconvert3>). Categories are RCB-0 (pCR), RCB-I, RCB-II and RC-III.
2. Objective tumour response according to RECIST criteria^31^, measured as % change from largest radiological diameter of target lesion at baseline to pre-surgery (mammography or magnetic resonance tomography). No more than two target lesion are measured, which are the largest measurable lesions within the breast. Categories are: complete response (CR, disappearance of all target lesions), partial response (PR, at least a 30% decrease in the sum of the largest diameter (LD) of target lesions, taking as reference the baseline sum LD), progressive disease (PD, at least a 20% increase in the sum of the LD of target lesions, taking as reference the smallest sum LD recorded since the treatment started or the appearance of one or more new lesions) and stable disease (SD, neither sufficient shrinkage to qualify for PR nor sufficient increase to qualify for PD, taking as reference the smallest sum LD since the treatment started).

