## Data management

All data are registered using an electronic Case Report Form (eCRF). Monitoring is performed according to Good Clinical Practice (GCP) guidelines. The eCRF provides data on age, demographics, background medical data, and initial tumour and lymph node characteristics deriving from clinical, radiological and histopathological assessment, details concerning type, dose and duration of neoadjuvant and adjuvant systemic therapy, as well as histopathological results at surgery and data on follow-up. Data are managed by the Clinical Trial Office at Centre for Clinical Cancer Studies, Karolinska University Hospital, Stockholm, Sweden. Security is comparable to bank security with encrypted data.

Recorded information is pseudonymised and the key kept at each responsible site. Keys may however need to be transferred to trial staff for quality assurance purposes such as central review of pathology slides and central review of imaging. Information is confidential and the database is privacy-protected; i.e., no data can be traced back to the patient in research reports and no unauthorized individuals may have access to the data about individuals in the database. The database will be maintained until further notice (at least 20 years after inclusion of the last patient) and be reported in accordance with General Data Protection Regulation (GDPR). The authority responsible for the database is Karolinska Institutet, Stockholm, Sweden.

The Neo-ACT trial is registered at www.clinicaltrials.gov (NCT05184582).

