## Statistical analysis plan

All outcomes will primarily be analysed using an intention-to-treat approach, i.e. all study subjects will belong to the treatment group (exercise intervention or control) they were assigned to, disregarding compliance. As sensitivity analysis, all outcomes will also be analysed using a per-protocol approach, meaning that participants in the intervention group who comply with less than 65% of the prescribed physical exercise program or complete less than 40% of the planned neo-adjuvant systemic therapy (around two 3-weekly courses) will be excluded from analysis.

*Covariate adjustment in statistical models*

Guidelines from the European Medicines Agency (EMA) regarding statistics and covariate adjustments recommend that factors that are used to stratify the randomization, i.e. site of treatment and biological tumour type in this trial, should be accounted for in the statistical analysis^35,36^. However, it is also recognized that “limited numbers of subjects per centre will make it impracticable to include the centre effects in the statistical model”. In this trial it is very likely that some of the centres will contribute few patients, which may cause problems in some of the statistical models, in particular for the categorical outcomes (such as the primary endpoint, pCR) where the variability in the outcome may be too small within each site. Hence, the statistical models, described below, will primarily be adjusted for biological tumour type and not for study site. If appropriate and if the data allows (i.e. no convergence problems and not too small subgroups), the site effect will also be incorporated in the models as a random effect in the mixed models and as a fixed factor in the remaining logistic regression models.

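### Mean tumour-size reduction is compared by ANOVA without baseline size, a minor and freely avoidable loss of precision in one supportive secondary analysis

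*Protocol*

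**What the plan says.** The sentence at issue closes the paragraph on objective tumour response (Protocol, Secondary endpoints): "Mean difference in reduction of tumour size between treatment arms will be analysed with an ANOVA, including biological subtype as a factor in the model". The covariate rule for all models, under Statistical analysis plan, adds nothing on baseline values: "the statistical models, described below, will primarily be adjusted for biological tumour type and not for study site". Site may be added if the data allow.

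The sentence gives no unit for reduction. Elsewhere the scale is a percentage. The endpoint is "measured as % change from largest radiological diameter of target lesion at baseline to pre-surgery" (Outcomes, Variables and measures), and the same paragraph opens by saying that RECIST will be used to "assess change in radiological tumour size (%) from baseline to pre-surgery imaging". The sentence just before the ANOVA brings in a second source of size: "Tumour size at histopathological assessment of the surgical specimen may be included in comparative analyses".

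On baseline size itself, the eCRF holds "initial tumour and lymph node characteristics deriving from clinical, radiological and histopathological assessment" (Data management), and eligibility is "Patients with primary invasive breast cancer cT1-T3 cN0-2" (Population). Stratification is by hospital and biological subtype only.

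**The concern.** When an outcome is a change from baseline, the baseline value is usually the covariate most worth having. Here it costs nothing, because a patient without a baseline diameter has no change to analyse. The cT1 to cT3 range means that diameters will vary widely, and randomisation does not balance them by design. If baseline size is related to the amount of reduction, leaving it out puts that variation into the error term, and a chance difference in size between arms moves the estimate.

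At stake is the precision of the trial's only continuous analysis of tumour response, since RCB and RECIST are otherwise analysed as ordered categories. Secondary outcomes are also tested at a Bonferroni-corrected level (Reporting), so precision is worth keeping.

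**Working it through.** **Inputs from the protocol.** The model is arm plus biological subtype. The protocol gives no power figure, SD or correlation for tumour size. Its only sample size is for pCR, with a "rate of the primary endpoint pCR will be approximately 30% in the control arm" against 40%, two-sided 5% and 80% power. Reproducing it:

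n per arm = [1.960·√(2·0.35·0.65) + 0.842·√(0.30·0.70 + 0.40·0.60)]² / 0.10² = (1.322 + 0.565)² / 0.01 ≈ 356, or 712 in total, as stated.

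That 712 is used below as the number analysed. Everything else is assumed.

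**General formula.** Adding baseline size multiplies the variance of the arm difference by about 1 − r², where r is the correlation of the outcome with baseline size within arm and subtype.

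**Millimetre scale, analytic.** With equal SDs at both times and correlation ρ between them, a change score has variance 2σ²(1 − ρ) and the ANCOVA residual has variance σ²(1 − ρ²). The ratio is (1 + ρ)/2:

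| ρ | variance ratio |
| --- | --- |
| 0.2 | 0.60 |
| 0.5 | 0.75 |
| 0.7 | 0.85 |

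**Simulation, both scales.** Assumptions:
- 712 patients, 1:1 within subtype, 1,500 runs per scenario
- log-normal baseline size, mean 30 mm, SD 14 mm
- subtype shares 45/20/10/25%, with mean reductions 40/60/75/70%
- residual SD 30 points, reduction capped at 100%
- proportional reduction either unrelated to size or lower by 5 or 10 points per SD of size
- a true effect of 0 or 6 points

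Power is at a nominal two-sided 5%, before any Bonferroni correction, for the 6-point effect.

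| % reduction versus size | mm: variance ratio | mm: power without → with baseline | %: variance ratio | %: power without → with baseline |
| --- | --- | --- | --- | --- |
| unrelated | 0.59–0.61 | 0.44 → 0.66 | 1.00 | 0.76 → 0.76 |
| −5 points per SD | 0.74–0.77 | 0.51 → 0.65 | 0.98 | 0.72 → 0.74 |
| −10 points per SD | 0.88–0.91 | 0.56 → 0.62 | 0.90 | 0.71 → 0.74 |

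A further set of simulations, also on assumed inputs, gave about 0.52–0.91 in mm. In % it gave 1.00 when shrinkage is unrelated to size and 0.82–0.95 when larger tumours shrink less. Taken together, the variance removed is roughly 10–50% in mm and 0–20% in %. By 1 − r², these correspond to r between √0.10 = 0.32 and √0.50 = 0.71 in mm, and between 0 and √0.20 = 0.45 in %.

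**Validity.** With no true effect, the unadjusted ANOVA rejected in 0.047 to 0.057 of runs on both scales, and its mean estimate was close to zero.

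**Chance imbalance.** With an assumed SD of 14 mm, the between-arm difference in mean baseline size has SD 14·√(2/356) ≈ 1.05 mm. One millimetre of imbalance moves the unadjusted estimate by about 0.2 to 0.55 mm on the mm scale, against a standard error of 0.76 to 0.90 mm. On the % scale it moves the estimate by 0 to −0.7 points, to the disadvantage of the arm with larger tumours, against a standard error of about 2.1 points. With baseline size in the model the shift is about zero on either scale.

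**The case against.** The strongest objection is about scale. A reader might infer that reduction is capped by baseline size, so that a small tumour that vanishes scores less than a large one that partly shrinks. That is true only in millimetres. The protocol defines the measure as percentage change, where every patient has the same 100% ceiling and a small tumour that vanishes scores the maximum. The large gains in the mm columns therefore cannot be claimed for the analysis the protocol most plausibly intends. This objection stands. What remains open is that the ANOVA sentence omits the unit and follows a sentence admitting pathological size, so a millimetre reading is not excluded.

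A reader might also infer that chance imbalance invalidates the comparison. It does not: type I error holds, there is no bias over randomisations, and an imbalance of about 1 mm moves the estimate by less than one standard error.

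Nor do the documents show that baseline diameter is measured in all randomised patients. The Study calendar lists no imaging, and only measurable breast lesions count. The supportable statement is that it exists for everyone who contributes this outcome.

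Finally, the covariate policy is reasoned, the main analysis of this endpoint is the ordinal regression of RECIST categories, and omitting a prognostic covariate from a valid analysis is a missed refinement. That is fair and sets the severity. It is no reason to keep the sentence, because the protocol itself names the method and the covariate, and adding baseline size cost essentially nothing in power in the simulated scenarios.

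**Conclusion.** The point holds as a minor one. The planned ANOVA is valid but less precise than it need be, and it leaves the realised estimate exposed to a chance difference in tumour size. On the protocol's percentage scale, adjustment removes about 0% to 20% of the variance. The gain is nil if proportional shrinkage is unrelated to size and appears only if larger tumours shrink proportionally less. In millimetres it would remove roughly 10% to 50%. Both ranges rest wholly on assumed SDs, correlations and shrinkage patterns, because the protocol supplies none.

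The missing unit should be settled in the same edit, since the scale decides which range applies. A reader might conclude that the outcome should become pre-surgery size in millimetres with baseline adjustment. The figures do not support that: it would replace the protocol's own measure, and in the tabulated scenarios the percentage analysis had more power (0.74 to 0.76 adjusted, against 0.62 to 0.66 for adjusted mm).

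Neither pCR nor the sample size of 712 is affected.

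**What to change.** Replace the ANOVA sentence under Objective tumour response with:

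> *Mean difference in % reduction in the radiological sum of largest diameters from baseline to pre-surgery will be analysed by ANCOVA with treatment arm, biological subtype and baseline sum of largest diameters (log-transformed if skewed); the adjusted mean difference and CI will be reported.*

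This keeps the percentage scale, names the size source and adds the covariate. If an absolute reduction in millimetres is also reported, it should use the same baseline adjustment. The cost is one sentence of wording, to be settled before the endpoint is analysed. It needs no new data, visits or patients.
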